### Study design

The HAPPEN study is a multicenter, two-arm, single-blind, prospective, randomized controlled trial initiated by the investigators of the HAPPEN collaboration group. In total, 600 AECOPD patients with low to moderate hypercapnic respiratory failure admitted to a network of 27 respiratory wards from university hospitals in China will be included and randomized to receive high-intensity or low-intensity NPPV. The protocol structure was written in compliance with the Consolidated Standards of Reporting Trials (CONSORT) 2010 statement guidelines, and it follows the Standard Protocol Items: Recommendations for Interventional Trials (SPIRIT) 2013 statement. The CONSORT diagram of the study is shown in Fig. 1, and the SPIRIT schedule for this trial is given in Fig. 2. The complete SPIRIT checklist for the study is provided in Additional file 1.

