### Randomization and blinding

Randomization will be accomplished by a computer-generated random number sequence, stratified by study center, with an allocation ratio of 1:1 for each group. The generation of sequences and their storage will be managed by an independent information technology expert who is not involved in this study. Each allocation sequence will be concealed from the coordinating center through the use of numbered, opaque, and sealed envelopes, and will be managed by an independent employee at the coordinating center who is not involved in this study. The randomization number will consist of a patient identification number of nine digits, in which the first four digits correspond to the identifier of the study center, the middle three correspond to the patient inclusion number at the respective center, and the remaining two correspond to the NPPV-strategy identifier. An independent telephone-contact system will be used for randomization. All investigators at each of the participating centers will immediately contact an independent employee of the coordinating center to obtain a randomization number if a patient fulfills the inclusion criteria. Within 1 h of the validation of the inclusion criteria, patients will be randomly assigned to undergo either high-intensity or low-intensity NPPV. Patients will continue to receive their current therapy prior to randomization assignment.

At each study center, at least two investigators will be conducting the study: one to perform the interventions defined in the protocol, and the other, who will be blinded to the intervention, to perform the data collection. All data related to the NPPV parameters will be extracted from a cloud platform by an independent information technology expert not involved in this study; all data analyses will be performed in a blinded fashion.

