### Sample-size calculations and interim analyses

The calculation of the sample size was based on our primary hypothesis that in AECOPD patients high-intensity NPPV leads to a reduced need for endotracheal intubation compared to low-intensity NPPV. Our previous clinical experience and previous studies [18–20] led us to anticipate that the need for endotracheal intubation would be 15% for the low-intensity NPPV group. Based on the assumption that the need for intubation could be reduced to 6% in the high-intensity NPPV group, we estimated that a minimum sample size of 480 patients would be required to detect a between-group difference of 9% for the need for intubation, with an 81% power and a two-tailed alpha level of 0.05, using superiority tests for two proportions. Assuming a dropout rate of 20%, we calculated that 600 patients should be enrolled.

Interim analysis to assess superiority is scheduled, and it will take place at hospital discharge of the first 300 randomized patients. The criteria for premature discontinuation of the study, based on the results of this single interim analysis, will be those defined by O’Brien and Fleming [34]. It will be performed at the coordinating center by an independent data and safety monitoring board (DSMB). The DSMB will meet by conference call, and DSMB discussions will take place by email or conference call.

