### Statistical analysis

We will report continuous variables as means ± standard deviations or medians and interquartile ranges, when appropriate, and categorical variables as proportions.

Continuous variables will be compared using an appropriate parametric (Student’s *t* test) or nonparametric (Mann–Whitney *U* test) method. Categorical variables will be compared using a chi-square test or Fisher’s exact test, if appropriate. A linear mixed model with two factors (study group and time) will be used to analyze variables repetitively measured over time; Bonferroni’s adjustment for multiplicity of tests will be used in post hoc comparisons to ensure that the total error rate will not exceed 0.05.

We will use a chi-square test or Fisher’s exact test to compare the primary outcome and secondary dichotomous outcomes, and a parametric (Student’s *t* test) or nonparametric (Mann–Whitney *U* test) method to compare secondary continuous outcomes, as appropriate. For the primary and secondary outcomes, we will calculate between-group differences in risk for dichotomous outcomes, between-group median differences (using Hodges–Lehmann estimates) for continuous outcomes with non-normal distributions, and between-group mean differences for continuous outcomes with normal distributions, all with 95% confidence intervals. The baseline characteristics will be tested for imbalance. If imbalances are found (despite the 1:1 randomization of a relatively large cohort), the primary and secondary outcome variables will be analyzed using a multiple logistic regression model, adjusted for possible baseline imbalances.

Cumulative event rates for the primary and secondary endpoints involving time-to-event data will be estimated for the two groups using the Kaplan–Meier method and compared using a log-rank test. Hazard ratios, their 95% confidence intervals, and *P* values for the comparison of the two treatment groups will be determined using the Cox regression model.

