The HAPPEN study protocol has limitations which must be addressed. First, the study is being performed in patients with mild to moderate respiratory acidosis, which suggests that the results may not be generalizable to the whole population. Further study will be required to assess whether our findings can be extended to other subgroups and the whole population. Second, despite the blinding of patients to the intervention, blinding of investigators is not possible due to the nature of the intervention, and this could induce bias. However, at each study center, at least two investigators will be working. One investigator will perform the interventions, as defined in the protocol. The second investigator, who will be blinded to the intervention, will collect data. Moreover, all data related with the parameters of NPPV will be extracted, and all data analyses will be performed in a blinded fashion. Third, even if protocol interventions represent a consensus among centers, between-center differences in the experience of NPPV use may still affect the results of this study. Fourth, several confounding factors associated with general therapy for AECOPD (e.g., the use of bronchodilators, corticosteroids, and antibiotics; fluid administration; thromboembolism prophylaxis; treatment of associated conditions) are only suggested and are not protocolized. Nevertheless, the study protocol stresses that general therapy is to be performed in accordance with each center’s specific expertise to ensure that the trial is as close as possible to routine clinical care.

In summary, the HAPPEN study will be the first randomized controlled study to investigate whether high-intensity NPPV better corrects hypercapnia and reduces the need for intubation and mortality in AECOPD patients than low-intensity NPPV. The results of the HAPPEN study will help critical care physicians choose the intensity at which to deliver NPPV to AECOPD patients.

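### Randomization is stratified by 27 centres but no planned analysis uses centre; the primary test stays valid but is mildly conservative if allocation is balanced within centre and centres differ

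*Protocol article*

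**What the plan says.** - **Design.** Under Randomization and blinding, the random sequence is "stratified by study center, with an allocation ratio of 1:1 for each group". Under Study design, patients are "admitted to a network of 27 respiratory wards from university hospitals in China". No block size or other restriction within centre is given.
- **Primary analysis.** Under Statistical analysis, the comparison is a chi-square or Fisher's "exact test to compare the primary outcome and secondary dichotomous outcomes". The effect measure is "between-group differences in risk for dichotomous outcomes" with a 95% confidence interval.
- **Other analyses.** The log-rank and Cox analyses name no strata. The mixed model has study group and time as its only factors.
- **Adjustment.** Only if baseline imbalance is found, the outcomes "will be analyzed using a multiple logistic regression model, adjusted for possible baseline imbalances". Centre is not mentioned there.
- **Limitations.** The Discussion says that "between-center differences in the experience of NPPV use may still affect the results of this study".

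**The concern.** Stratifying by centre removes chance differences between the arms in their mix of centres. If centre is prognostic, the treatment comparison then varies less than a simple two-sample formula assumes. A test and interval that ignore centre keep the larger standard error. The test rejects less often than 5% under the null, the interval is wider than it need be, and some power is lost.

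The conditional adjustment does not cover this. It is triggered by imbalance, whereas stratification exists to keep centre balanced. The gain comes from centre being prognostic.

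Centre differences in the primary endpoint are plausible on the article's own account. The final intubation decision rests with the attending physician (NPPV weaning and failure), and general therapy follows each centre's routine (General therapy for AECOPD). The primary test is named in the text, so this is a stated choice rather than a detail left to a separate analysis plan.

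**Working it through.** **Inputs from the article.** There are 27 centres and 600 patients enrolled. In the planning assumptions "the need for endotracheal intubation would be 15% for the low-intensity NPPV group" and "the need for intubation could be reduced to 6% in the high-intensity NPPV group". Alpha is 0.05, two-sided.

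**Assumptions, not in the article.** Centres are of equal size. Allocation is exactly 1:1 within centre. Centre effects are normal on the logit scale with SD 0, 0.5, 1.0 or 1.2, and the overall event rates are held fixed.

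**Step 1: the plan's own figures.** 480 / (1 − 0.20) = 600, so the dropout inflation reproduces. The 81% power for 480 patients does not: the pooled two-proportion formula gives 89.8% for 15% vs 6% at 240 per arm. That is a separate matter with no bearing on this point.

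**Step 2: why the plain test is conservative.** Let p be the overall rate, p_k the rate in centre k, and ρ = Var(p_k) / [p(1 − p)]. Under the null with 1:1 allocation in every centre:

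- variance used by the plain test: 4p(1 − p)/N
- actual variance: 4p(1 − p)(1 − ρ)/N

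The plain test therefore behaves like a normal test with critical value 1.96/√(1 − ρ). At p = 0.15:

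- SD 0.5 gives ρ ≈ 0.032; 1.96/√0.968 = 1.992, a two-sided level of about 0.046.
- SD 1.0 gives ρ ≈ 0.116; 1.96/√0.884 = 2.085, a level of about 0.037.

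**Step 3: simulation.** 27 centres × 22 patients = 594, 11 per arm in each centre, 60,000 trials per cell. Each cell gives the rejection rate for plain chi-square / centre-stratified Cochran-Mantel-Haenszel (CMH).

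| Centre SD | Null, 15% vs 15% | Planned, 15% vs 6% | Smaller effect, 15% vs 8% |
|---|---|---|---|
| 0 | 0.051 / 0.050 | 95.7% / 95.7% | 77.3% / 77.1% |
| 0.5 | 0.047 / 0.051 | 95.7% / 95.8% | 77.5% / 78.1% |
| 1.0 | 0.038 / 0.049 | 95.9% / 96.5% | 78.1% / 80.6% |
| 1.2 | 0.034 / 0.049 | 96.1% / 97.0% | 78.2% / 81.9% |

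A separate run of 40,000 trials gave 0.047, 0.038 and 0.036 for the plain test under the null at SD 0.5, 1.0 and 1.2. Across runs, the loss at 15% vs 6% is about 0.1, 0.6 and 0.8–0.9 points. At 15% vs 8% it is about 0.6, 2.5–2.6 and 3.5–3.7 points.

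**Step 4: interval width.** With 600 patients, 15% vs 6% and blocks of four (assumed), the mean width of the plain interval against the Mantel-Haenszel interval is:

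- SD 0.5: 0.0967 vs 0.0959, 0.8% wider
- SD 1.0: 0.0964 vs 0.0928, 3.9% wider

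**Step 5: no restriction within centre.** With 594 patients allocated by simple randomization in each centre, the plain test keeps its level (0.050 at SD 0 and at SD 1.0). With identical centres CMH then costs power at 15% vs 6%: 95.6% falls to 94.7% with 594 patients, and 91.2% to 89.5% with 486 (27 × 18). At SD 1.0 and 594 patients CMH is ahead, 95.9% against 95.1%.

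**The case against.** The case for leaving the plan alone is a fair one.

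- **The error is on the safe side.** A reader might infer that ignoring the strata biases the estimate or makes the 5% test invalid. It does neither: false positives are not inflated. This objection stands in full.
- **Within-centre balance is not stated.** The article gives a computer-generated sequence, stratified and 1:1, without a block scheme. If allocation is unrestricted, the plain interval is not over-wide. This stands as a condition on the point. Stratifying by centre does little unless allocation is restricted within centre, so balance is the natural reading, but it needs confirming.
- **The size depends on unknown heterogeneity.** No between-centre variation is reported. A reader might take the interval to be too wide outright, but the text supports this only if centres differ. At SD 0.5 or below the effect is negligible.
- **At the planned effect little power is at stake.** The losses of several points arise at 15% vs 8%, an effect the article does not plan for. They show sensitivity to a smaller true effect and are not the planned loss.
- **The limitation can be overread.** The article says that centre experience may affect results, not that the authors expect it to. If experience alters the treatment effect itself, a stratified test would not resolve that.

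What survives is that centre was made a design factor and appears in no planned analysis. Under blocked allocation, using it costs essentially nothing.

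**Conclusion.** The point holds as a modest efficiency recommendation. Its size rests on two conditions that the article does not settle: allocation balanced within centre, and real differences between centres in intubation risk. With both, the plain analysis is conservative by the amounts shown above: under one power point at the planned effect and 600 patients for SDs up to 1.2, and more if the true effect is smaller. With balanced allocation and no centre differences, the two analyses are equivalent. The documents do not support any claim of bias, invalidity or excess false positives.

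**What to change.** - Pre-specify a Cochran-Mantel-Haenszel test stratified by centre as the primary test, with a Mantel-Haenszel risk difference and 95% confidence interval.
- Set in advance a rule for pooling very small centres. At 600/27 ≈ 22 patients per centre on average, some may be small.
- Stratify the log-rank and Cox analyses by centre.
- Keep the unstratified chi-square or Fisher's test as a supporting analysis.
- State whether allocation is blocked within centre. If it is not, weigh the choice again: the plain test then holds its 5% level, and CMH costs about 1 to 2 power points when centres are alike.

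The cost is analysis wording. Centre is already coded in the first four digits of each patient number, so no new data and no change in trial conduct are needed. The change should be made before any unblinded result is seen, including the interim analysis at 300 patients.

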### Endpoints and follow-up

The primary endpoint is the NPPV failure rate, defined as the need for endotracheal intubation and invasive ventilation at any point during the study. Secondary endpoints include decrement of PaCO_2_ from baseline to 2 h after randomization, hospital mortality, 28-day mortality, and 90-day survival, as well as actual intubation rate, intensive care unit (ICU) admission, hospital stay, hospital costs, ventilator-free days within 28 days, hospital-free days within 90 days, and 90-day hospital readmission.

All patients will be monitored until hospital discharge or until day 90 in cases where the patients remain at the hospital. After discharge, follow-up will be performed by phone on days 28 and 90 after randomization, and the following will be recorded: 28-day mortality, ventilator-free days within 28 days, hospital-free days within 90 days, 90-day survival, and 90-day hospital readmission.

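### If hospital costs are skewed, the plan gives no mean cost difference, only a Hodges–Lehmann shift that estimates something else

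*Protocol article*

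**What the plan says.** All references are to the protocol article.

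- **Endpoints and follow-up** lists among the secondary endpoints "hospital stay, hospital costs, ventilator-free days within 28 days, hospital-free days within 90 days".
- **Statistical analysis** offers Student's t test or Mann–Whitney as the "method to compare secondary continuous outcomes, as appropriate". When an outcome is not normal, the promised estimate is "between-group median differences (using Hodges–Lehmann estimates) for continuous outcomes with non-normal distributions". When it is normal, the section instead promises "between-group mean differences for continuous outcomes with normal distributions, all with 95% confidence intervals".
- **Sample-size calculations and interim analyses** assumes that "the need for endotracheal intubation would be 15% for the low-intensity NPPV group" and that "the need for intubation could be reduced to 6% in the high-intensity NPPV group".

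No separate rule is given for costs. They fall under the general rule for continuous outcomes, and a mean difference is reported only if they look normal.

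**The concern.** For costs, the arithmetic mean is the quantity that multiplies up to total spend. The Hodges–Lehmann estimate is the median of all between-arm pairwise differences. It equals the mean difference only if one arm's distribution is the other's moved by a constant, or if both distributions are symmetric. When the shapes differ, it need not equal the difference in medians either, so the label the article gives it is inexact.

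A change in the share of patients who are intubated alters the upper tail of the cost distribution. It does not move the whole distribution by a constant. If intubated patients are much more expensive, the planned estimate can therefore be well below the mean saving even when the trial succeeds as designed. Because the measure depends on a look at the distribution, which cost quantity will be reported is also unknown until the data are in.

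**Working it through.** **Inputs from the article.** Intubation 15% v 6%, a difference of 9 percentage points. The 480 evaluable patients give 240 per arm, and the 600 enrolled give 300 per arm (480/0.8 = 600 reproduces). The article has no cost figure, so there is none to reproduce. How 480 was derived does not bear on this point.

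**Assumed inputs.** Cost without intubation is log-normal with median 1 and log-SD σ = 0.4, 0.6 or 0.8. Cost with intubation is R = 2, 3, 5 or 8 times as high, with the same σ. At first the arms differ only in the intubation rate.

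**Step 1: mean saving.** With m = exp(σ²/2), mean cost is m[1 + 0.15(R − 1)] in the low-intensity arm and m[1 + 0.06(R − 1)] in the high-intensity arm. The difference is 0.09(R − 1)m. As a share of the low-intensity mean it is 0.09(R − 1)/[1 + 0.15(R − 1)]:

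- R = 2: 0.09/1.15 = 7.8%
- R = 3: 0.18/1.30 = 13.8%
- R = 5: 0.36/1.60 = 22.5%
- R = 8: 0.63/2.05 = 30.7%

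**Step 2: Hodges–Lehmann shift.** This is the d that solves P(X − Y > d) = 0.5, where X is a low-intensity and Y a high-intensity cost. It was solved numerically for the two mixtures. Units are the median non-intubated cost, and each cell gives σ = 0.4 / 0.6 / 0.8.

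| R | Mean saving | Hodges–Lehmann | Share of mean saving |
|---|---|---|---|
| 2 | 0.097 / 0.108 / 0.124 | 0.055 / 0.057 / 0.055 | 57 / 53 / 44% |
| 3 | 0.195 / 0.215 / 0.248 | 0.071 / 0.083 / 0.084 | 37 / 39 / 34% |
| 5 | 0.390 / 0.431 / 0.496 | 0.076 / 0.102 / 0.111 | 20 / 24 / 22% |
| 8 | 0.682 / 0.754 / 0.868 | 0.077 / 0.108 / 0.126 | 11 / 14 / 15% |

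Simulated trials give the same shares to within about two points (43–55%, 34–38%, 20–24%, 11–14%). The mean saving grows about sevenfold from R = 2 to R = 8, since (8 − 1)/(2 − 1) = 7, while the shift stays between 0.055 and 0.126. At σ = 0.4 and R = 8 the difference in medians is 0.061 and the shift 0.077, so the two are not the same quantity.

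**Step 3: a general saving as well.** Suppose every high-intensity cost is also multiplied by 0.9 (assumed). The mean saving becomes m[0.10 + 0.096(R − 1)]. Hodges–Lehmann then shows between 72% of it (σ = 0.4, R = 2: 0.152 of 0.212) and 20% (σ = 0.8, R = 8: 0.210 of 1.063).

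**Step 4: power.** Suppose the effect runs only through intubation and every intubated patient costs more than every other patient. Then P(X > Y) = 0.15 × 0.94 + 0.5 × (0.15 × 0.06 + 0.85 × 0.94) = 0.545. The standard error is √(2/(12n)), which is 0.0264 at 240 per arm and 0.0236 at 300.

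- 240 per arm: 0.045/0.0264 = 1.71, and power is Φ(1.71 − 1.96) ≈ 40%.
- 300 per arm: 0.045/0.0236 = 1.91, and power is Φ(1.91 − 1.96) ≈ 48%.

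In the simulated scenarios at 240 per arm, Mann–Whitney has 13–39% power and a Welch comparison of means 14–83%. At σ = 0.8 and R = 2 the two are almost equal (13% v 14%). With the 10% general saving of Step 3, the two powers lie within about 3 percentage points of each other in every cell.

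**The case against.** Four objections deserve weight.

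1. **The mechanism.** A reader might infer that the trial's hypothesis acts only through the 9% of patients spared intubation, so that a rank method nearly misses the effect. The article does not say so. The 15% and 6% serve to size the primary endpoint. The Background and Discussion describe a broader mechanism: better alveolar ventilation, less work of breathing, more comfort. This objection stands. Without that restriction the power ceiling of Step 4 goes, and Mann–Whitney is not a weak test here. Even with the restriction, the description of a near miss fits cost ratios of 5 or more, not 2 or 3.
2. **The other endpoints.** A reader might extend the point to hospital stay, ventilator-free days and hospital-free days. The total-spend argument does not carry over to them. Rank methods are legitimate there, and nothing calculated here shows harm.
3. **No economic aim.** Costs appear once, late in the list of secondary endpoints, and not in the aims or the abstract. This limits the importance of the point. It does not change what the planned estimate means.
4. **A condensed article.** A cost-specific method could sit in the full protocol or analysis plan. But the article does not leave the matter open: it states which measure a non-normal outcome receives, and costs fall under that rule.

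**Conclusion.** The point stands for hospital costs only, and it is about the estimand. If costs are non-normal, the plan as written would not estimate the difference in mean cost. Its estimate would show about 44–57% of the mean saving at a cost ratio of 2, falling to 11–15% at 8, if only intubation changes. With a 10% saving in every patient it would show 20–72%.

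These sizes rest on assumed skew, cost ratios and log-normal shape; the article supplies none of them. What does not depend on those figures is that a mixture change from 15% to 6% is not a pure shift, so the two measures have no reason to agree. Low power is not a general fault of the plan: the ceiling of about 40% (240 per arm) or 48% (300 per arm) applies only if the effect runs solely through intubation. Costs are a secondary endpoint, and the primary conclusion is unaffected.

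**What to change.** In the Statistical analysis section, add one sentence: hospital costs will be compared as the difference in arithmetic means with a bootstrap 95% confidence interval, whatever their distribution, and medians will be given as description only. Leave hospital stay, ventilator-free days and hospital-free days as planned.

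The cost is that sentence and a bootstrap run; no new data are needed. The downside is small: a mean is more sensitive to a few very expensive stays, which the width of the bootstrap interval will reflect.

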### Data collection and definitions

At each study center, patient data will be collected using that center’s dedicated pseudonymous CRF, and the CRFs will be stored in locked file cabinets in areas with limited access. Data will be transmitted to the coordinating center whenever a patient dies or is discharged from the hospital, and follow-up data will be transmitted to the coordinating center when follow-up is complete. In addition, the coordinating center will have direct access to the cloud platform to extract the data related to the NPPV parameters. Before the data are exported into a computerized database at the coordinating center, two trained data collectors from the coordinating center will check the completeness and quality of information. Logical checks will be performed for missing data and to determine inconsistencies. If required, the data collector will contact the investigator by phone to validate or reformat the data for entry into the database. Then all data entry will be performed separately by two trained data collectors, and their work will be checked by another two collectors. Only the principal investigator and the data managers at the coordinating center will have access to the final database.

At enrollment, patients’ baseline characteristics will be recorded: demographics, medical history, history of NPPV use, history of steroids and/or inhalation therapy use, smoking status, spirometry (forced ventilatory capacity and forced expiratory volume in 1 s), Acute Physiology And Chronic Health Evaluation (APACHE) II score, vital signs (including heart rate, RR, arterial blood pressure, SpO_2_), dyspnea score, scale for the use of accessory muscles, Glasgow coma scale (GCS) score, arterial blood gases (including pH, PaO_2_, PaCO_2_, bicarbonates, and lactates), and routine laboratory tests (including hemoglobin, white blood cell count, platelet count, prothrombin time, partial thromboplastin time, creatinine, blood urea nitrogen, alanine aminotransferase, aspartate aminotransferase, and bilirubin).

At 2, 6, 24, and 48 h after randomization, vital signs, dyspnea score, scale for the use of accessory muscles, GCS score, supplemental oxygen flow, and arterial blood gases will be recorded.

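### The adjustment rule picks covariates by testing for baseline imbalance, then assigns logistic regression to all primary and secondary outcomes, including continuous ones that it cannot fit

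*Protocol article*

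**What the plan says.** The Statistical analysis section of the protocol article first sets unadjusted comparisons. The primary outcome and the dichotomous secondary outcomes get a chi-square or Fisher test with a risk difference. A t test or Mann–Whitney test is the "method to compare secondary continuous outcomes, as appropriate", with a mean or Hodges–Lehmann difference.

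The adjustment rule follows: "The baseline characteristics will be tested for imbalance". If a difference is found, "the primary and secondary outcome variables will be analyzed using a multiple logistic regression model, adjusted for possible baseline imbalances". No covariates are named, and the sentence is not limited to binary outcomes.

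The next paragraph gives Kaplan–Meier, log-rank and Cox methods for time-to-event endpoints.

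Under Endpoints and follow-up the list reads "Secondary endpoints include decrement of PaCO_2_ from baseline to 2 h after randomization, hospital mortality, 28-day mortality, and 90-day survival", and goes on to include "hospital stay, hospital costs, ventilator-free days within 28 days, hospital-free days within 90 days". The PaCO2 decrement and these last four are continuous or counts of days.

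**The concern.** The rule has three defects as written.

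- **Model and outcome do not match.** Binary logistic regression needs a two-valued outcome, and five of the listed secondary outcomes are not two-valued. The analyst would have to depart from the protocol or choose cut-points, possibly after seeing the data.
- **The covariates are chosen by chance.** After proper randomization, a significant baseline difference is a chance finding, and its P value says nothing about how strongly the variable predicts outcome. Weak predictors can enter the model while strong ones that happen to be balanced stay out.
- **The status of the adjusted result is open.** It is not said whether it replaces the unadjusted result or stands beside it. For the primary endpoint the two also use different effect measures, a risk difference and an adjusted odds ratio.

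A lesser matter is that the PaCO2 change is compared without a baseline covariate, although baseline PaCO2 is collected.

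**Working it through.** The plan gives no figure of its own on this point, so there is none to reproduce.

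**1. Outcome types against the stated model**

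| Outcome | Type | Logistic regression usable? |
|---|---|---|
| NPPV failure (primary) | binary | yes |
| Hospital and 28-day mortality, actual intubation, ICU admission, 90-day readmission | binary | yes |
| 90-day survival | binary or time-to-event | yes if binary; Cox is already stated if time-to-event |
| PaCO2 decrement to 2 h | continuous | no |
| Hospital stay, hospital costs | continuous | no |
| Ventilator-free and hospital-free days | counts of days | no |

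As a check, a binary logistic fit was attempted on a simulated continuous outcome; the software rejected it because the outcome was not between 0 and 1.

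**2. How often the trigger would fire by chance**

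The baseline list under Data collection and definitions has about k = 30 items, counting demographics and medical history once each. The level α = 0.05 is the general threshold in the Statistical analysis section; that it applies to each baseline test is an assumption.

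- Expected chance differences: kα = 30 × 0.05 = 1.5. This does not depend on independence.
- Probability of at least one, if independent: 1 − 0.95^30 = 0.785.
- Sensitivity to the count: 1 − 0.95^20 = 0.642; 1 − 0.95^40 = 0.871.
- If correlation made the list behave like 15 independent tests (an assumption): 1 − 0.95^15 = 0.537.

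**3. Two effect measures for the primary endpoint**

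At the planning rates of 15% and 6%, the risk difference is −9 percentage points. The unadjusted odds ratio is (0.06/0.94)/(0.15/0.85) = 0.0638/0.1765 = 0.36. These are different quantities, so the report needs to know which one leads.

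**4. Precision for PaCO2 at 2 h**

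Assume equal variance σ² at baseline and 2 h, with correlation ρ. The documents do not give ρ. Per-patient variance is 2σ²(1 − ρ) for the change score and σ²(1 − ρ²) for ANCOVA, so the ratio ANCOVA/change is (1 + ρ)/2.

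| Assumed ρ | Ratio | Reduction in variance |
|---|---|---|
| 0.3 | 0.65 | 35% |
| 0.5 | 0.75 | 25% |
| 0.7 | 0.85 | 15% |
| 0.9 | 0.95 | 5% |

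**5. Error rates**

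Trials were simulated with no effect, 240 patients per arm and 10,000 runs per ρ. Test-then-adjust here means ANCOVA only when baseline PaCO2 differs at P < 0.05.

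| ρ | Change-score t test | Test-then-adjust | Always ANCOVA | Change score when baseline P is 0.05–0.20 |
|---|---|---|---|---|
| 0.5 | 5.1% | 4.3% | 5.0% | 9.6% |
| 0.7 | 5.1% | 4.7% | 4.9% | 8.8% |
| 0.85 | 5.3% | 5.0% | 5.4% | 7.0% |

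Overall error is not inflated under any of the three approaches. The last column is conditional on a subset of randomizations.

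**The case against.** Much can be said for the plan, and several stronger readings do not survive.

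- **The primary result is compromised.** A reader might infer two competing primary answers. The chi-square or Fisher test of the primary outcome is stated without any condition, and logistic regression is a proper model for that endpoint. What stands is that the adjusted result is never labelled as supportive.
- **The model is also wrong for survival times.** The next paragraph of the same section already gives Cox regression for time-to-event endpoints, so this does not hold.
- **The trigger will nearly always fire.** The 79% needs independent items. Many overlap: pH, PaCO2 and bicarbonate; creatinine and urea; the two transaminases; the two spirometry values; and a severity score beside its likely components. The true probability is probably lower, and the documents do not allow it to be computed.
- **Comparing PaCO2 change scores is an error.** It is not. In a randomized trial the comparison is valid and keeps its error rate, as the simulation shows. Whether the mixed model uses baseline PaCO2 is a detail that an article may leave to the analysis plan.

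It is also fair to say that a full covariate list usually sits in the analysis plan. Its absence is not the point here. The article states a selection rule and a model, and both are unsuitable as worded.

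**Conclusion.** The point holds in a limited form. Logistic regression cannot be applied to the continuous secondary outcomes as the text directs, and this follows from the wording alone. The covariate rule makes the adjusted analysis data-dependent: 1.5 chance differences are expected among about 30 items at 0.05, and the probability of at least one is about 79% under independence and probably less in practice. The relation between the adjusted and unadjusted results is left open.

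Baseline adjustment of PaCO2 is a gain in precision, not a correction. Its size rests on an assumed correlation and on equal variances.

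Severity is should-fix, because the stated primary test remains valid.

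**What to change.** Change the Statistical analysis section as follows:

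1. Delete the tests of baseline imbalance and the conditional trigger; describe baseline data without P values.
2. State that the chi-square or Fisher test is the primary analysis of NPPV failure and that adjusted analyses are supportive.
3. Prespecify a small covariate set from data already collected, for example baseline pH, PaCO2 and APACHE II score, and use it whatever the observed balance. Account for study center, the only stratification factor. The planning rates imply 300 × 0.15 + 300 × 0.06 = 63 events over 27 centers, about 2.3 per center, so a random intercept or a stratified method is safer than 26 fixed center terms.
4. Use logistic regression for binary outcomes only, the Cox model already stated for time-to-event outcomes, and a linear or other model suited to the distribution for the continuous ones. Name the model for each outcome.
5. As an optional gain, analyze 2-h PaCO2 by ANCOVA with baseline PaCO2 and arm.

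The cost is wording only, since the suggested covariates are already recorded at enrollment. The article describes recruitment as ongoing, so the change should be dated before any unblinded results are seen, including those of the interim analysis at 300 patients.
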